#### Blinding

This study was carried out in an unblinded fashion. Blinding of study staff and participants was not feasible given the distinct protocols and timelines of the two study arms, including procedures for assessment of outcomes.

#### Data collection: smartphone technology

Quantitative data from both index and partner participants are collected by health advisors via smartphones using the Open Data Kit (ODK) platform. Pre-generated questionnaires programmed using ODK are downloaded from the NASCOP database and administered to participants. To optimize data consistency and accuracy at entry, completed questionnaires are uploaded over an encrypted connection to the NASCOP server immediately after the interview. Data verification and analysis are conducted weekly to ensure rapid, reliable data quality control and assurance.

#### Intimate partner violence monitoring

Due to concerns that HIV APS could lead to IPV for index cases, safeguards and monitoring for IPV were incorporated into the study protocol. IPV refers to physical, sexual, or psychological harm by a current or former partner or spouse, which can occur among heterosexual and same-sex couples [18]. We consulted IPV experts and community organizations regarding how to identify, counsel, and refer participants with a current or past history of IPV.Health advisors were trained according to a specific IPV screening protocol.

During screening, all potential participants are evaluated according to an IPV rating system that classifies them as low, moderate, or high risk. Individuals at high risk of IPV (reported IPV within the last 1 month) are not eligible for the study and are referred to IPV centers for counselling. We defined individuals at low risk IPV as: 1) no history of IPV during their lifetime either from a current or past partner; and 2) no fear of IPV if they participate in the study. These participants undergo standard study procedures and follow-up IPV case reports at 6 weeks and 3 months to capture any interim violence. Moderate risk IPV individuals were defined to have the following: 1) a history of IPV during their lifetime either from a current or past partner; and/or 2) fear of IPV if they participate in the study. Moderate risk participants receive additional special monitoring through scheduled phone calls or home visits at 10, 20, and 30 days after enrolment, as well as referral to IPV counselling and treatment centers identified *a priori* for further evaluation and management. Reports of IPV during the course of the study will be assessed on a case-by-case basis by the safety committee for further guidance. Internal monitoring for IPV is conducted through weekly data audits and IPV reports. The study safety committee, with representation from the study funder, conducts bi-annual meetings to monitor study progress and any reported IPV.

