#### Partner notification services

The timeline and components of partner notification in the intervention arm (immediate APS) and control arm (delayed APS) are displayed in Figure 3. At sites randomized to immediate APS, health advisors encourage index participants to disclose their HIV status to sexual partners and tell them that they will be contacting their partners within the next 1–2 weeks, consistent with provider referral [17]. At sites randomized to delayed APS, health advisors encourage index participants to disclose their HIV status to sexual partners (passive referral) as per HTC guidelines; health advisors then contact partners 6 weeks after index case enrollment.

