**Figure 3 Fig3:**
[figure not shown]
**Study flow for intervention versus control sites, starting from when an index participant tests HIV-seropositive.** Illustrated here are the study procedures for the intervention arm (immediate APS following index participant enrollment) and the control arm (APS delayed for 6 weeks after index participant enrollment). The star (*) indicates that the partner services involve: 1) partner tracing and enrollment; 2) HIV testing and counselling of partners; and 3) referral of HIV-seropositive partners to HIV care.

Partners are first contacted via phone. To enhance credibility and create a safe space for the ensuing conversation, health advisors introduce themselves as Ministry of Health health-care workers based at KNH, the principal National Referral Hospital in Kenya. If partners ask how their contact information was obtained, they are told that it was obtained from a NASCOP database. In the original protocol, health advisors disclosed that a sexual partner had provided the contact information, without revealing the identity of the index participant. However, partners often declined to participate unless they knew who identified them. The script was changed after the first month to facilitate enrollment while protecting the confidentiality of index participants. This was the only change made to methods after trial commencement.

Health advisors then inquire whether the partner is in a suitable environment for health information to be discussed. If so, health advisors engage in a discussion about the partner’s health status, especially recent sexual contacts, risky sexual behavior and possible exposure to HIV. For individuals who are not in a suitable environment to discuss their health status, another phone call is planned or an in-person interview is scheduled.

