On the phone or in person, health advisors encourage HIV testing and describe study objectives and the consent process. Partners are invited to speak with the health advisor and test for HIV at a study site close to their location. For those who cannot come to a study site, health advisors arrange a meeting at a convenient place and time; these have included partners’ homes, workplaces, or other public areas. When health advisors meet partners, they introduce themselves again, producing staff identification badges if necessary, and obtain written informed consent for the study. HTC is then performed. Health advisors provide HIV testing to those who agree, and HIV prevention counselling to those who decline. Confidentiality is emphasized throughout the process, and the partner is assured that their information will not be shared.

If a partner cannot be reached by phone after four attempts, the health advisor travels to his/her home or work and discreetly finds a way to speak to the partner in private so that confidentiality is maintained. They then describe the study as detailed above. If a partner still cannot be found after physical tracing, the health advisor verifies the contact information with the index participant and attempts to trace again. Failed physical tracing (at least three attempts), partners with insufficient contact information, and successfully traced partners who decline study participation are documented. Due to resource constraints, partners residing >50 km from the study site are notified via phone call, and if they cannot attend a study site for enrolment, they are not enrolled but still strongly encouraged to test at the nearest HTC facility.

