#### Participant follow-up

Index cases participate in three study visits: one at baseline for screening/enrolment and two follow-up visits at 6 weeks and 3 months to assess linkage to HIV care, IPV and other social harms, and risk behaviors.

Partners in the immediate APS arm participate in two visits: one at baseline for recruitment and a follow-up visit after 6 weeks to determine whether they have tested for HIV and linked to care if HIV-seropositive. Linkage to care is verified by any of the following: CCC registration number, CD4 count, WHO HIV staging, or commencement of co-trimoxazole and/or ART. Partners in the delayed APS arm have a single visit scheduled at 6 weeks after enrollment of the index, which serves as a combined recruitment and assessment for any prior notification, HIV testing, and linkage to care if HIV-seropositive.

All participants are reminded via phone call on the day prior to a scheduled visit. Any participants who miss appointments are traced by health advisors (by phone, at home, or at work) and rescheduled. Any participants who cannot be traced at the closure of each study site (after approximately 6-months duration) are considered lost to follow-up.

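### In the delayed arm, all three extra violence checks for moderate-risk index participants fall before partners are due to be contacted

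*Protocol article*

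**What the plan says.** The section Intimate partner violence monitoring gives the reason for the safeguards: "Due to concerns that HIV APS could lead to IPV for index cases, safeguards and monitoring for IPV were incorporated into the study protocol". It sorts potential participants into low, moderate and high risk. High-risk people are excluded. Low-risk people follow the standard schedule, with "follow-up IPV case reports at 6 weeks and 3 months to capture any interim violence". Moderate-risk people, who have a lifetime history of IPV or fear it if they take part, also receive "additional special monitoring through scheduled phone calls or home visits at 10, 20, and 30 days after enrolment" and a referral to an IPV centre. The schedule is counted from enrolment and is not split by arm.

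The section Partner notification services fixes when partners are approached. In the immediate arm, index participants are told that "they will be contacting their partners within the next 1–2 weeks". In the delayed arm, "health advisors then contact partners 6 weeks after index case enrollment". Study design gives the same 6-week delay. Participant follow-up gives index participants "two follow-up visits at 6 weeks and 3 months to assess linkage to HIV care, IPV and other social harms".

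**The concern.** The extra contacts exist because assisted notification might provoke violence, and they go to the people judged more vulnerable to it. Counting them from enrolment suits the immediate arm, where notification follows enrolment closely. In the delayed arm the special contacts end before staff are due to approach any partner. A moderate-risk participant there goes through provider notification with no special contact afterwards. Nobody may be scheduled to ask about resulting violence for six to seven weeks, so help may come late.

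The stake is participant safety. The primary outcomes, the power and the 6-week comparison between arms are not touched.

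**Working it through.** The plan gives no figure to reproduce. The check is calendar arithmetic on its stated schedule.

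**Inputs**
- Special contacts: days 10, 20 and 30 after enrolment (Intimate partner violence monitoring).
- Delayed-arm partner contact: 6 weeks = 6 × 7 = day 42 (Partner notification services; Study design).
- Immediate-arm partner contact: 1–2 weeks = days 7 to 14 (Partner notification services).
- Index visits that assess IPV: 6 weeks = day 42, and 3 months (Participant follow-up). I take 3 months as days 84 to 91, which is an assumption.

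**Delayed arm, special contacts.** They fall 42 − 10 = 32, 42 − 20 = 22 and 42 − 30 = 12 days before planned partner contact. Special contacts after it: 0 of 3.

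**Delayed arm, wait to the next check.** The 6-week visit is 42 − 42 = 0 days after contact, so it cannot be relied on to capture the consequences. The 3-month visit is 84 − 42 = 42 to 91 − 42 = 49 days after. If tracing takes a further 1–2 weeks (an assumption, since the plan gives that interval only for the immediate arm), contact falls on days 49 to 56. The wait is then 84 − 56 = 28 to 91 − 49 = 42 days.

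**Immediate arm**

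| Partner contact | Special contacts, days after it | 6-week visit, days after it |
|---|---|---|
| Day 7 | 3, 13, 23 | 35 |
| Day 14 | −4, 6, 16 | 28 |

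So two or three special contacts follow partner contact.

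**Slow tracing.** Staff may need repeated calls and then travel ("If a partner cannot be reached by phone after four attempts, the health advisor travels to his/her home or work"), so immediate-arm contact can slip past day 14. One special contact is left if first contact falls on days 20–29, and none from day 30. Even so, the longest wait to the next scheduled check for any contact before day 42 is short: at most 10 days for contact on days 0–29, and 42 − 30 = 12 days for contact on days 30–41.

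**Effect of the proposed calls.** They fall on days 42 + 10 = 52, 42 + 20 = 62 and 42 + 30 = 72. The wait to the first check drops from 42–49 days to 10. The third call precedes day 84 if contact occurs by day 53 (53 + 30 = 83). Contact on day 56 puts it on day 86, inside the 3-month window.

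**The case against.** The strongest reply is that counting from enrolment is sensible. All index participants have just tested positive and are encouraged to disclose from the start. In the delayed arm, self-disclosure is the only planned route of notification for six weeks. It identifies the index participant, whereas staff use a script that conceals the source: "The script was changed after the first month to facilitate enrollment while protecting the confidentiality of index participants". The early calls therefore cover a real hazard period, including partners brought in early, which Study limitations reports. This stands, and it is why the early calls should stay. It does not cover a later staff approach to a partner to whom the index participant has not disclosed. Concealing the source lowers that risk but may not remove it.

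A second reply is that this is a condensed article and an unseen IPV protocol may contain a delayed-arm schedule. It is true that coverage of both arms is inferred, because the section names neither. But the article is not silent: it states exact days and an exact starting point, and on those terms the period after notification has no special contact.

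Third, other safeguards continue: exclusion of high-risk people, referral, weekly data audits, case-by-case committee review and the look-back at 3 months. A 6-week visit that is rescheduled late could also fall after partner contact. Staff may return to the index participant to verify locator details. All of this limits the harm, but none of it is a scheduled special contact after notification.

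Fourth, the Discussion reports that by submission no fresh or aggravated partner violence had been attributed to APS. The concern is precautionary for that reason.

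Finally, an immediate-arm participant whose partner is first reached on or after day 42 would face the same wait. That is fair, and it is a refinement of the remedy.

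**Conclusion.** The point holds. As planned, 0 of the 3 special contacts in the delayed arm follow partner contact. The next scheduled IPV check clearly after it is 42 to 49 days away, or 28 to 42 days if tracing takes 1–2 weeks. Any partner contact before day 42 is followed by a scheduled check within 12 days at most. This rests on reading the special schedule as common to both arms, on nominal visit timing, and on 3 months meaning days 84 to 91.

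This delays detection and support for a group the plan itself marked as vulnerable; detection is not lost altogether. The article does not say how many delayed-arm participants were at moderate risk. It is worth correcting as an inexpensive safety improvement, with no bearing on the efficacy conclusions.

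**What to change.** Keep the day 10, 20 and 30 contacts in both arms. IPV ascertainment then stays equal over the first 6 weeks, with three calls plus the 6-week report in each arm. For moderate-risk delayed-arm index participants who have not yet reached partner contact, add special calls about 10, 20 and 30 days after a health advisor first contacts one of their partners. If tracing pushes the third call to the 3-month visit, let the visit replace it. The immediate-arm schedule can stay as it is; the same trigger could optionally serve anyone there whose first partner contact falls on or after day 42.

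The cost is up to three calls per affected participant, made by existing health advisors. At the planned minimum of 9 × 60 = 540 delayed-arm participants the ceiling is 540 × 3 = 1,620 calls, reached only if all were at moderate risk and none had yet reached partner contact. Trial status says all 18 sites were already running, so the actual number would be smaller.

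The one downside is that the delayed arm would have more IPV checks than the immediate arm after week 6. IPV counts from week 6 to month 3 should therefore not be compared between arms. APS is due in both arms by then, and the comparison over the first 6 weeks is unchanged.

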### Outcome measures

Outcomes will be compared between intervention and control arms based on data collected 6 weeks after enrollment of index participants and will be analyzed at the cluster level.

Primary outcomes are as follows: 1) HIV testing of partners (number of partners of an index participant that were tested for HIV, offset by the number of partners with locator information provided by the index participant); 2) newly identified HIV-infected partners (number of partners of an index participant identified as HIV-infected, offset by the number of partners of that index participant who were HIV tested); and 3) linkage to HIV care (number of partners of an index participant who were linked to HIV care, offset by the number of partners of an index participant identified as HIV-infected; analysis will be limited to index participants with at least one HIV-infected partner).

Secondary outcomes are as follows: 1) the incremental cost per HIV-infected person identified and linked to care, including ART, and the incremental cost-effectiveness per incident HIV infection, HIV-related death, and disability adjusted life-year (DALY) averted in Kenya from payer and societal perspectives; and 2) costs of identifying >1 partner per index case.

There have been no changes to outcome measures.

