**Methods/design:**

Eighteen sites were selected among health facilities in Kenya with well-established, high-volume HIV testing programs, to reflect diverse communities and health-care settings. Restricted randomization was used to balance site characteristics between study arms (*n* = 9 per arm). Sixty individuals testing HIV positive (‘index partners’) will be enrolled per site (inclusion criteria: ≥18 years, positive HIV test at a study site, willing to disclose sexual partners, and never enrolled for HIV care; exclusion criteria: pregnancy or high risk of intimate partner violence). Index partners provide names and contact information for all sexual partners in the past 3 years. At intervention sites, study staff immediately contact sexual partners to notify them of exposure, offer HIV testing, and link to care if HIV seropositive. At control sites, passive partner referral is performed according to national guidelines, and assisted partner notification is delayed by 6 weeks. Primary outcomes, assessed 6 weeks after index partner enrollment and analyzed at the cluster level, are the number of partners accepting HIV testing and number of HIV infections diagnosed and linked to care per index partner. Secondary outcomes are the incremental cost-effectiveness of partner notification and the costs of identifying >1 partner per index case. Participants are closely monitored for adverse outcomes, particularly intimate partner violence. The study is unblinded due to practical limitations.

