The primary objective of the study is to evaluate the effectiveness of HIV APS in Kenya for HIV case-finding and linkage to care among sexual partners of index cases. We hypothesize that APS will increase HIV testing, new HIV diagnoses, and linkage to care among HIV-positive partners compared to passive referral, and that case-finding will be enhanced by extending APS beyond the primary partner to other sexual partners. We also predict that HIV APS will be acceptable with minimal social harms, and that APS will be cost-effective from both payer and societal perspectives. A cluster-randomized design was selected to minimize risk of contamination between arms and to evaluate barriers in implementation and program costs at the facility level. Outcomes will be analyzed at the cluster level. Examining challenges and outcomes across diverse study sites will provide insights into best practices to help guide APS implementation.

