### Statistical methods and analysis

For the primary outcomes, generalized estimating equations models with a Poisson link will be used to compare intervention and control arms at 6 weeks post-enrollment of index participants. The use of these models will allow analysis of data at the cluster level.

Cost-effectiveness analyses will follow the WHO guidelines [19] and use mathematical models to simulate the health outcomes from study data and to consider clinical outcomes beyond the scope of the study. Using the outcomes and costs from the study and effectiveness (health outcomes) estimated by the model, the cost-effectiveness will be estimated. To estimate effectiveness of APS compared to existing passive partner notification, a compartmental, deterministic disease progression and transmission model for HIV based on previous HIV and STI models will be used [20]. The model will be parameterized by data from population-based studies in Kenya and the literature and validated using Kenyan demographic health survey and antenatal data. The model will be used to predict the potential impact of APS on HIV incidence, progression, and mortality. Sensitivity and scenario analyses will account for uncertainty in parameters including varying impact of APS on identifying new HIV cases. Incremental costs for the intervention and treatment costs incurred (and averted) as a result of the intervention will be estimated in comparison to existing passive partner notification and HIV-care costs. Using these estimates of APS effectiveness and incremental cost of APS per HIV-positive person identified and treated, the incremental cost-effectiveness ratio per incident HIV case, HIV-related death, and DALY averted will be calculated.

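### Primary outcomes 2 and 3 are offset by counts that APS itself changes, so they measure positivity and linked fraction rather than the per-index yield stated in the abstract

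*Protocol article*

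**What the plan says.** The protocol article states the primary outcomes in two places.

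- **Abstract, Methods/design.** After partners accepting a test, the outcome is the "number of HIV infections diagnosed and linked to care per index partner". There, index partners are the enrolled people who tested HIV positive.
- **Outcome measures.** Outcome 1 is partners tested, "offset by the number of partners with locator information provided by the index participant". Outcome 2 is the "number of partners of an index participant identified as HIV-infected, offset by the number of partners of that index participant who were HIV tested". Outcome 3 is partners linked to care, "offset by the number of partners of an index participant identified as HIV-infected", and the "analysis will be limited to index participants with at least one HIV-infected partner". The section adds that outcome measures have not changed.

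For analysis, Statistical methods and analysis says that "generalized estimating equations models with a Poisson link will be used to compare intervention and control arms" for the primary outcomes.

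The objective in the Background is to "evaluate the effectiveness of HIV APS in Kenya for HIV case-finding and linkage to care among sexual partners of index cases". The hypothesis is that "APS will increase HIV testing, new HIV diagnoses, and linkage to care among HIV-positive partners compared to passive referral". The Discussion repeats the case-finding aim: the trial is meant to show whether APS finds more people who did not know they were HIV positive than passive referral does.

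**The concern.** In a Poisson model with a log link, an offset of log(D) turns the arm coefficient into a ratio of events per unit of D. With D equal to partners tested, outcome 2 compares positivity among those tested. With D equal to partners found infected, outcome 3 compares the share linked among those found. Neither is a count of people found, or found and linked, for each index participant enrolled.

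APS is intended to change both denominators, and both arise after randomisation. The comparison is therefore between sets of partners that the arms have selected differently, and randomisation does not protect it.

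Two of the three primary results could be read as showing no benefit, or harm, on case-finding and linkage when APS had found and linked more people. The abstract and the methods would also support different readings of the same data.

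**Working it through.** **Inputs from the article.** Sample size and power analysis gives a control rate of 0.1 partners tested per index participant, a twofold increase, between-site coefficient of variation k = 0.25, 60 index participants per site and 9 sites per arm. That is 9 × 60 = 540 index participants per arm. The Discussion reports 50% positivity among tested partners and 85% linkage among positives in the Cameroon programme. For the Malawi trial it reports 51% v 24% of partners tested and 64% positivity among those tested. The Cameroon and Malawi figures serve only as illustrations.

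**The plan's own figure.** The standard Hayes–Moulton formula for unmatched rates gives c = 1 + (1.96 + 0.84)² × [(0.1 + 0.2)/60 + 0.25² × (0.1² + 0.2²)] / (0.1)² = 1 + 7.85 × 0.8125 = 7.38, so 8 sites per arm against the 9 stated. The article uses an adapted form that it does not show, and 9 is on the safe side. Nothing below depends on the difference. The calculation covers testing only.

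**Identity.** Ratio for outcome 2 = (ratio of cases found) / (ratio of partners tested).

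**Planned effect, equal positivity (50%, 85% linked).**

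| Quantity | Control | APS | Ratio |
|---|---|---|---|
| Partners tested | 540 × 0.1 = 54 | 540 × 0.2 = 108 | 2.0 |
| Found infected | 27 | 54 | 2.0 |
| Linked | 23 | 46 | 2.0 |
| Diagnoses per index participant | 0.05 | 0.10 | 2.0 |
| Linked per index participant | 0.0425 | 0.085 | 2.0 |
| Outcome 2 as defined | 27/54 = 0.50 | 54/108 = 0.50 | 1.0 |
| Outcome 3 as defined | 0.85 | 0.85 | 1.0 |

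**Range.** If cases found double, outcome 2 shows 2 / (testing ratio): 2.0, 1.6, 1.33, 1.0 and 0.8 for testing ratios of 1, 1.25, 1.5, 2 and 2.5.

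**Simulation** (9 sites × 60 per arm; site variation of 0.25 on testing, none on positivity).

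- Testing doubled, 50% positivity: outcome 2 was significant in 5% of 20,000 runs, against 71% for diagnoses per index participant. A second model, with an assumed 1.3 named partners per index participant, 80% linkage and 200 runs, gave 3% against 76%. In that model outcome 3 had ratio 1.01 (5.5% significant), while linked cases per index participant had ratio 1.96 (63%).
- Malawi testing proportions, 64% positivity in both arms (200 runs): outcome 2 ratio 1.00; diagnoses per index participant 2.08.
- Hypothetical fall in positivity from 60% to 40% as testing doubles: by arithmetic, outcome 2 is 0.40/0.60 = 0.67, and diagnoses per index participant rise by 2 × 0.67 = 1.33. In 200 runs the outcome 2 ratio was 0.66 and significant in 69%.
- Testing unchanged, positivity doubled from 30% to 60% (200 runs): outcome 2 ratio 2.03, so the effect is seen.

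**Who enters the analysis if the model is fitted per index participant.** With Poisson counts, 540 × (1 − e^−0.1) = 51 control and 540 × (1 − e^−0.2) = 98 APS index participants have a tested partner. At 50% positivity, 540 × (1 − e^−0.05) = 26 and 540 × (1 − e^−0.1) = 51 have an infected one. The rest have log(0) as offset in outcome 2 and drop out, although the text states a restriction only for outcome 3. These counts rest on a control rate that the article calls conservative. With the Malawi testing proportions, about 156 and 308 index participants had a tested partner in simulation.

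**The case against.** The three outcomes can be read as successive steps of a cascade: tested, positive if tested, linked if positive. The sample size section names testing as the primary hypothesis and powers only that. Outcome 1 would show the rise in testing, and the secondary cost per person identified and linked draws on absolute yield. For outcome 3, the hypothesis speaks of linkage among HIV-positive partners, which is literally the linked fraction. The article also says repeatedly that analysis is at cluster level. If counts are summed by site, about 6 and 12 tested partners are expected per site, and a zero offset would be rare.

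Most of this stands as a limit on the point, and it rules out three stronger readings that a reader might infer.

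- *Any doubling of case-finding would be missed.* Not so. The null result needs the gain to come through testing at similar positivity. If positivity rises, outcome 2 shows an effect.
- *Self-motivated testers in the passive arm are more often positive, so the result will be reversed.* No section says this. The 64% and 50% in the Discussion come from two different studies and do not describe passive and assisted arms. A reversal is possible but hypothetical.
- *Most index participants are certain to be lost from outcome 2.* That depends on fitting the model per index participant. The outcome definitions point that way and the cluster-level statements point the other, so the text does not settle it.

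What the objection does not answer is the conflict between the abstract and Outcome measures. Nor does it make positivity among tested partners a measure of case-finding. Summing by site leaves the denominators post-randomisation.

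**Conclusion.** The point holds in conditional form. As defined, outcomes 2 and 3 estimate a positivity ratio and a linked-fraction ratio, each conditional on counts that APS changes. Both conflict with the per-index outcomes in the abstract. Outcome 2 also conflicts clearly with the case-finding aim in the Background and Discussion. Outcome 3 agrees with one reading of the hypothesis.

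Under the article's own mechanism, a doubling of testing, and with equal positivity, outcome 2 is centred on 1.0 with about a 3% to 5% chance of significance. Diagnoses per index participant double, with a 71% to 76% chance of being significant. The size rests on the planned rates, on 50% positivity in both arms and on site variation in testing only. The trial as a whole is not blind to the effect, because outcome 1 would detect the rise in testing. The defect is that the two outcomes meant to carry case-finding and linkage do not carry yield.

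**What to change.** Reconcile the abstract, the Background and Outcome measures by a documented amendment, decided without reference to outcome data by arm.

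- **Outcome 2:** number of partners newly diagnosed per enrolled index participant.
- **Outcome 3:** number of partners newly diagnosed and linked to care per enrolled index participant.
- **For both:** keep every enrolled index participant, keep zeros, and use no post-randomisation offset.
- **Outcome 1:** state it consistently with the abstract, since it too carries an offset (partners with locator information) that the abstract does not mention.
- **Descriptive:** report positivity among tested partners and linkage among diagnosed partners by arm as cascade measures, without treating them as randomised comparisons.

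No new data are needed. The cost is more than wording. The trial is unblinded and, per Trial status, the intervention had reached all 18 sites with data collection under way, so the date of and reason for the change must be recorded. The linkage count will also no longer isolate the linkage step, which stays visible in the descriptive measures.
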